## Abstract

Transcranial direct current stimulation (tDCS) has been shown to have the potential to improve the motor recovery of the affected upper limbs in patients with stroke, and recently, several optimized tDCS methods have been proposed to magnify its effectiveness. This study aims to determine the effectiveness of personalized tDCS using brain MRI-based electrical field simulation and optimization, to enhance motor recovery of the upper limbs in the patients. This trial is a double-blind, randomized controlled trial in the subacute to chronic rehabilitation phase. Forty-two adult stroke patients with unilateral upper limb involvement will be randomly allocated to three groups: (1) personalized tDCS with MRI-based electrical field simulation and optimized stimulation, (2) conventional tDCS with bihemispheric stimulation of the primary motor cortex, and (3) sham tDCS. All three groups will undergo 10 intervention sessions with 30 min of 2-mA intensity stimulation, during a regular upper limb rehabilitation program over two weeks. The primary outcome measure for the motor recovery of the upper limb impairment is the Fugl–Meyer assessment for the upper extremity score at the end of the intervention, and the secondary measures include changes in the motor evoked potentials, the frequency power and coherence of the electroencephalography, performance in activities of daily living, and adverse events with a 1-month follow-up assessment. The primary outcome will be analyzed on the intention-to-treat principle. There is a paucity of studies regarding the effectiveness of personalized and optimized tDCS that considers individual brain lesions and electrical field characteristics in the real world. No feasibility or pivotal studies have been performed in stroke patients using brain MRI, to determine a lesion-specific tDCS simulation and optimization that considers obstacles in the segmentation and analysis of the affected brain tissue, such as ischemic and hemorrhagic lesions. This trial will contribute to addressing the effectiveness and safety of personalized tDCS, using brain MRI-based electrical field simulation and optimization, to enhance the motor recovery of the upper limbs in patients with stroke.

## 1. Introduction

Many patients complain of upper limb paralysis, which remains, in many cases, as a disability that interferes with the independence of daily living [1]. These motor impairments of the upper limbs would be known to relate to the corticospinal tract (CST) integrity, originating from the primary motor cortex [2,3]. In addition, the cerebellar afferent and efferent tracts also contribute to the motor function of the upper limbs [4,5]. Combining this knowledge for the anatomical basis of the upper limb motor function, the primary motor cortex and CST are the most critical structures for the motor function of the upper limbs. Thus, previous studies for noninvasive neuromodulation via repetitive transcranial magnetic stimulation (rTMS) or transcranial direct current stimulation (tDCS), have targeted the ipsilesional primary motor cortex for enhancing the motor function of the upper limbs [6,7,8].

Proper treatment and effective recovery in patients with a stroke are important issues for the patients themselves, their families, neurologists, therapists and physiotherapists. Many stroke survivors have ongoing impairments of the upper limbs [9]. Recently, noninvasive brain stimulation has been introduced to reduce the impairments of the upper limbs [8,10,11]. Among the various types of noninvasive brain stimulation, transcranial direct current stimulation (tDCS) is being actively studied [12,13]. The tDCS has recently received the most attention because of its safety, convenience, and portability [12,14,15] A constant, low-intensity current (1 to 2 mA) is passed through two electrodes placed over the head and modulates the neuronal activity [16,17]. The widespread opinion is that anodal stimulation increases the cortical excitability, whereas cathodal stimulation reduces the cortical excitability (by hyperpolarization and depolarization, respectively) [18].

The level of evidence for tDCS is still low because a standardized protocol has not been fully established [19]. Particularly, this is because the results of studies that tried to verify the tDCS effects were inconsistent [20], and a main factor was the large variation in the treatment effect between individuals, even when the same protocol was applied [21]. High levels of interindividual variations in the tDCS effects are thought to be because the low-intensity current transmitted through the scalp is influenced by the brain structure, such as the characteristics of brain anatomy [22]. As a result, these inconsistent findings have been taken as a lack of evidence for its effectiveness [23,24]. Although a 10–20 EEG guide was introduced to apply tDCS electrodes in a manner that considers the variation in individuals’ head geometry, the guide did not provide an exact match for the patients’ brains in clinical neurorehabilitation settings.

Recently, some studies have attempted to define the optimized stimulation parameters and to reveal the mechanisms of interaction between the electric field (E-field) induced by tDCS and the cortical neurons and their therapeutic effects [22]. The lack of an analytical and technical pipeline enabling the optimization of stimulation parameters across individuals is a factor that interferes with the accumulation of evidence. Optimization methods requiring the analysis of individual MR images to make a brain model and the calculation of E-fields induced by tDCS, is very labor intensive, and there is an inconvenience in using multiple types of research software. These reasons have blocked the application of tDCS with the calculated E-fields in the clinical setting. Thus, we recently developed a method that analyzes the magnetic resonance image of an individual, to generate a brain model and then calculates the magnitude of the electric field generated by tDCS, through the analysis of the brain structure, in a single software package [25]. To maximize the effect of tDCS, not only the individual brain structures but also the stroke lesions must be considered [26], so the software was developed to include methods that could segment the stroke lesions and calculate the conductivity of the stroke lesions. One previous study reported that the optimized electrode montages which applied MRI-based individual head models for tDCS, could yield the maximal stimulation target, compared to conventional montages [27]. However, the study has no results about the clinical effect.

Taking into account the mentioned limitations of the conventional tDCS method and the results of a previous study, our ongoing development of optimized software, and current clinical demands, we hypothesized that MRI-based optimized personalized tDCS would be better than conventional tDCS, to treat patients with a stroke for improving the upper limb function. Thus, we will investigate the efficacy of the MRI-based optimized personalized tDCS for improving the upper limb function in patients with a subacute and chronic stroke via a multicenter prospective randomized double-blinded controlled trial. We present the rationale and precise methods from our planned trial: MRI-based personalized transcranial direct current stimulation to enhance the upper limb function in patients with a stroke: A randomized double-blinded controlled trial. The proposed protocol seeks to establish the benefits from personalized anodal tDCS with two control groups, a sham control group and a conventional anodal tDCS group, to prove the treatment efficacy of the upper limb motor function in patients with a stroke.

## 2. Materials and Methods

### 2.1. Trial Design

This trial design is a prospective randomized placebo and actively controlled (using sham-tDCS and conventional-tDCS), a parallel group, double-blind, multicenter, phase 2 feasibility study (Figure 1). A personally optimized tDCS (opt-tDCS) will be compared to the sham-tDCS or conventional-tDCS (con-tDCS) in patients with a subacute to chronic stroke. All interventions are performed with the usual rehabilitation, such as occupational therapy, physical therapy, and peripheral functional electrical stimulation.

### 2.2. Participants Involvement and Ethics Approval

This protocol was approved by the Korean Ministry of Food and Drug Safety and complied with the ethical standards, based on the Declaration of Helsinki. The final protocol was approved by the Ethics Review Boards of the Catholic University (approval number: VC21DIDS0085) and the National Traffic Injury Rehabilitation Hospital (approval number: NTRH-21004). Written informed consent will be obtained from each participant.

### 2.3. Recruitment

Participants will be screened and recruited from two hospitals: The Catholic University of Korea, St. Vincent’s Hospital and the National Traffic Injury Rehabilitation Hospital in Republic of Korea.

### 2.4. Inclusion and Exclusion Criteria

The *inclusion criteria* are as follows: (1) age over 19 years old; (2) stroke confirmed by brain MR images; (3) first-onset stroke; (4) subacute or chronic phase (at least 4 weeks after the stroke onset); (5) unilateral upper limb paralysis; (6) an upper extremity FMA score (out of 66) of 56 or less; and (7) capacity to understand the explanation of this clinical trial, voluntary participation and written agreement to abide by the precautions.

The exclusion criteria will be the following: (1) those with a disease that may affect the function of the paralyzed arm, such as recurrent stroke, traumatic brain injury, spinal cord injury, degenerative brain disease, such as Parkinson’s disease, or upper extremity nerve injury; (2) those who cannot conduct clinical trials according to the instructions, due to cognitive decline; (3) those who have severe communication difficulties, due to total aphasia; (4) those with evidence of delirium, confusion or other disturbances of consciousness; (5) those with an uncontrolled medical or surgical disease; (6) those who cannot undergo tDCS due to scalp disease; (7) those who have metallic substances (e.g., clip, coil, or metabolic foreign body) in the brain; (8) those with pacemakers or cochlear implants; (9) those who have used stimulation devices that are similar to the medical devices used in this clinical trial, within at least 1 year, or have experience in participating in related clinical trials; (10) those with severe neurological disorders accompanying major psychiatric disorders; (11) those with a history of epilepsy; (12) those who have medical contraindications to brain imaging acquisition; (13) those who have taken prohibited concomitant medications or need to change medications that may affect their cognitive and motor function changes, through changes in brain activation during the study period (however, this does not apply to those who are taking the drug in a stable manner); and (14) pregnant or lactating women and those who plan to become pregnant during the clinical trial period.

### 2.5. Enrollment and Randomization

Participants who meet all the inclusion criteria and none of the exclusion criteria and have given informed consent, will be evaluated by the investigators for enrollment. At enrollment, the information will be collected, including the demographic data, body measurements, stroke history, complications, and baseline function measures. The investigator will verify that the patient is eligible to participate and enter information into the electric data capture and web allocation system, as required.

The participants will be randomly assigned to a personally optimized tDCS group (opt-tDCS), a conventional tDCS group (con-tDCS; an active control group), or a control group (sham-tDCS) in a 1:1:1 ratio, in the order of registration. To minimize the effects, based on the disease severity, a Fugl–Meyer assessment for the upper extremities (FMA-UE) cutoff values were used to divide patients into 0–34 (moderate to severe) and 35–56 (mild to moderate) groups, and the onset period was used to stratify patients into two groups, subacute (onset 1–6 months) and chronic (greater than 6 months). Statisticians who were not otherwise involved in this clinical trial used statistical software to randomize the randomization numbers, according to the block randomization method. The issued randomization number was put in a randomization bag and delivered to the medical device manager of each site. The allocation sequence was concealed from an independent researcher. A sealed envelope was given to the coordinator of the physical therapy area to identify the group for each participant.

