### 2.8. Primary Outcome

Upper limb functional changes will be evaluated by the FMA-UE scores, between the baseline and postintervention, at 2 weeks. The FMA-UE is a performance-based impairment index, including the motor function with a range of motion and sensation in patients with a stroke, and the results are represented as a numerical score with a maximum of 66 points [27,29].

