### 2.11. Statistical Analyses

The descriptive statistics (average, standard deviation, median, minimum, and maximum) are presented for each group for the change in the primary outcomes at 2 weeks, compared to the baseline (0 weeks), and the comparison of differences between the groups will be the repeated measures ANCOVA that considers time as a covariate. If statistically significant changes were confirmed in the comparison of the differences between the three groups, a repeated ANCOVA that considered the timing of the differences between the two groups (e.g., opt-tDCS and con-tDCS, opt-tDCS and sham-tDCS) was planned as a post hoc analysis. The results corresponding to the secondary outcomes will be presented as descriptive statistics (frequency, ratio) for each group, based on the change in score at 4 weeks, and the difference between the two groups, will be analyzed using the repeated measures ANCOVA, that considers time.

The primary outcome will be analyzed in the intention-to-treat population, and the safety outcomes will be analyzed in the per-protocol population. No protocol interim analysis is planned, and a total of 42 patients will be enrolled in this clinical trial over a total of 30 months. This sample will be able to evaluate the clinical applicability of the optimized tDCS treatment in the subacute to chronic stages of a stroke and aims to verify the trends in the intergroup differences and the changes to demonstrate the statistically significant differences in the upper limb function improvement between the two groups.

The outcome analysis of this trial will be largely divided into a safety set (SS) group, a full analysis set (FAS) group, and a per-protocol set (PP) group. The efficacy evaluation will analyze the PP group as the main analysis group and analyze the FAS group. If the results are different across the analysis groups, the results of each analysis method will be presented and analyzed to identify the reason. The safety assessment will be carried out in the SS group, and the significance level will be set at 0.05.

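### The analysis model names neither of the two stratification factors; to the extent that they predict the 2-week change, the test is conservative and loses power

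*Protocol article*

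**What the plan says.** Section 2.5 (Enrollment and Randomization) allocates to three arms "in a 1:1:1 ratio, in the order of registration". Its stated purpose is "To minimize the effects, based on the disease severity", and FMA-UE "cutoff values were used to divide patients into 0–34 (moderate to severe) and 35–56 (mild to moderate) groups". For the second factor, "the onset period was used to stratify patients into two groups": subacute (1 to 6 months) and chronic (more than 6 months). The numbers were generated "according to the block randomization method"; no block size is given.

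The primary outcome in section 2.8 is the change in "FMA-UE scores, between the baseline and postintervention, at 2 weeks".

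Section 2.11 (Statistical Analyses) says that "the comparison of differences between the groups will be the repeated measures ANCOVA that considers time as a covariate". The post hoc pairwise comparisons, run only if the three-group comparison is significant, and the secondary outcomes get the same kind of model, again with only time or timing named. Onset phase, the severity band and baseline FMA-UE as a covariate appear in none of the three statements. The significance level is 0.05.

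**The concern.** Stratified blocks keep the arms nearly balanced on severity band and onset phase, so differences between strata largely drop out of the arm contrast. A model without the strata still counts those differences as residual error. The estimate is then more precise than its reported standard error, and the test rejects less often than its nominal level allows.

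This matters here because there are 14 patients per arm and because the three-group test is the gate to the pairwise comparisons. A needlessly conservative gate can stop the trial from reaching optimised versus conventional and optimised versus sham, which are the comparisons it was set up to make.

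**Working it through.** **Inputs from the article.** 42 patients in three arms, so 42/3 = 14 per arm (sections 2.5 and 2.10). Two factors with two levels each, so 4 strata (2.5). Significance level 0.05 (2.11). Section 2.10 gives no effect size, SD or power, so there is no planned figure to reproduce.

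**Assumptions.** Two-sided test; half of the patients subacute; within-stratum SD of the change set to 1; mean change differing between onset groups by D; blocks of 3 or 6.

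**Step 1: SE inflation.** With half of the patients in each onset group, the between-group variance is D² × ½ × ½ = D²/4. The model without strata uses residual variance 1 + D²/4. Under near-balance, the arm contrast actually varies as if that variance were 1. So:

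SE ratio = √(1 + D²/4), and the share of variance due to onset is R² = (D²/4)/(1 + D²/4).

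- D = 0.5: √1.0625 = 1.03; R² = 0.0625/1.0625 = 0.06
- D = 1.0: √1.25 = 1.12; R² = 0.25/1.25 = 0.20
- D = 1.5: √1.5625 = 1.25; R² = 0.5625/1.5625 = 0.36

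**Step 2: level and power of the three-group test.** Simulation of the change score: 4 strata, blocks of 3, 4000 runs per setting, effect of 1 within-stratum SD in the optimised arm. An F test without strata is compared with one adjusted for both factors.

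| D | True level without strata | Power without strata | Power with strata | Loss (points) |
|---|---|---|---|---|
| 0.5 | 4.5% | 71% | 74% | 3 |
| 1.0 | 2.9% | 64% | 76% | 12 |
| 1.5 | 1.1% | 52% | 75% | 23 |

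A repeat simulation with blocks of 3 gave levels of 4.7%, 2.7% and 1.0%, and power of 73%, 64% and 51% without strata against 75%, 75% and 74% with them. Blocks of 6 gave levels of 4.1%, 2.5% and 1.4%, and power of 72%, 64% and 53% against 74%, 74% and 75%. At D = 0 the two analyses agreed to within about 1 point. Simulation error on a power near 75% is √(0.75 × 0.25/4000), or about 0.7 points.

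**Step 3: a second scale.** Here the total SD is 1, the contrast is pairwise, blocks are of 6 and the effect is 1.0 total SD. The strata explain a share R² of the variance in change.

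| R² | Mean model SE / true sampling SD, no strata | Type I error, no strata | Power, no strata → with strata |
|---|---|---|---|
| 0 | 0.376 / 0.378 | 0.051 | 0.73 → 0.72 |
| 0.2 | 0.378 / 0.336 | 0.026 | 0.74 → 0.82 |
| 0.3 | 0.379 / 0.321 | 0.018 | 0.76 → 0.87 |
| 0.5 | 0.381 / 0.281 | 0.008 | 0.78 → 0.95 |

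At R² = 0.2 the SE ratio is 0.378/0.336 = 1.125, in line with the 1.12 of step 1. With both factors in the model, the SE matches the sampling SD (0.338 against 0.333 at R² = 0.2) and the type I error is 0.050. Power losses differ from step 2 because the effect is scaled to the total SD and the test is pairwise.

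**Step 4: which model term removes the loss.** With scores at baseline and 2 weeks, the group-by-time test is a comparison of change scores. A between-patient main effect adds the same amount to both scores and cancels in the change. In a mixed model fitted to simulated data (42 patients, onset affecting change), the group-by-time SE was 0.532 without onset, 0.532 with onset as a main effect, and 0.401 with onset-by-time added.

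**The case against.** **It is a matter for the SAP.** A condensed article need not list every covariate, and section 2.11 does not say that the strata are excluded. This has some force, and an unseen SAP may include them. But the article does not leave the covariate open: it states the model three times and names only time. If the SAP has the strata, the article should agree with it. If not, the problem is real.

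**The size is assumed.** This stands. Nothing in the article says how strongly severity or onset predicts a 2-week change. At D = 0.5 the loss is only 2 to 3 points, and the larger losses need onset alone to explain 20% to 36% of the variance. Analysing change already removes differences in baseline level, so what remains is the strata's effect on the change itself. Section 2.5 speaks only of limiting effects of disease severity; it does not say that recovery depends on onset phase.

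**Stronger readings that the article does not support.** A reader might infer that a true level different from 0.05 makes the test invalid, but the departure is on the safe side. A reader might infer that power is certainly lost, but the loss vanishes if the strata are not prognostic. A reader might infer that a planned power is missed, but section 2.10 states none and calls the trial exploratory. Finally, it is tempting to think that entering onset phase as one more fixed factor in the repeated measures model would cure the problem. Step 4 of the working shows that it would not.

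**Conclusion.** The point holds in conditional form. The article stratifies by two factors and then specifies a model that names neither. If the strata predict the 2-week change, the three-group, pairwise and secondary tests are all conservative and less powerful than they need be.

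For onset differences of 0.5 to 1.5 within-stratum SD, the SE is about 3% to 25% too wide. The true level of the three-group test falls to between about 4.5% and 1.1%, and about 3 to 23 points of power are lost for a 1 SD effect. These figures rest on an even split by onset, small blocks, 42 analysed patients and an analysis of change. The losses are relative to an adjusted analysis of the same data. This is an efficiency flaw that should be corrected, not a threat to validity.

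**What to change.** Choose one of two specifications and state it in section 2.11 and the SAP:

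- **ANCOVA of the 2-week FMA-UE score (or of the change)**, with arm, baseline FMA-UE as a continuous covariate (or the severity band if the continuous value is not used) and onset phase.
- **The repeated measures model with its group-by-time test**, with severity-by-time and onset-by-time terms added. Main effects alone are not enough.

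Use the same terms in the pairwise and secondary models, and fix them before unblinding so that the choice cannot look data-driven.

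The cost is a sentence of text and 1 to 2 of the 42 − 3 = 39 residual degrees of freedom. Both variables are already recorded for randomisation. If the strata turn out not to be prognostic, the price in power is about 1 point or less.

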### 2.6. tDCS Treatment, Simulation and Blinding

#### 2.6.1. tDCS Device

Participants will undergo an intervention tDCS treatment using a battery-driven and portable device (Neurophet innk, Neurophet, Seoul, Republic of Korea), programmed to deliver either active or sham tDCS. The device delivers 2.0 mA (with 30 s for ramping up and ramping down; Figure 2) of the direct current through the two sponge-coated electrodes (electrode size: 5 × 5 cm^2^). The tDCS device used in this study can check the impedance values occurring in patient’s skin, in real time, during all tDCS sessions. If an impedance above 13 kOhm occurs, the stimulation is stopped, and the medical device investigator confirms the patient’s condition and skin. This may reduce the adverse events that may occur on the patient’s skin, due to the increased impedance. In the sham-tDCS condition, the device delivers 120 s of the current, including 30 s for ramping at the beginning and end of each session, to maintain the blinding procedure. The tDCS treatment was performed 10 times over a total of 2 weeks, and sham-tDCS was also applied 10 times with sham stimulation for 2 weeks. Following this duration, both opt-tDCS and con-tDCS groups, but not the sham-tDCS group, will receive the opportunity to provide additional written consent for an extension study; if the participants give consent, the extension study will be conducted for two additional weeks. During the 2 or 4 weeks of intervention, if there was a usual rehabilitation program that was being performed before participation in this study, the program and frequency could be continued without any changes. The detailed intervention methods regarding tDCS for each group, is as follows (Figure 3a). The representative figure which represents the difference between optimized tDCS and conventional tDCS simulation results in participant is Figure 3b.

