### 2.7. Blinding

In the case of this study, it is difficult to keep the examiner blinded because the location of the tDCS electrodes is different, depending on the treatment method. Therefore, an unblind investigator, in charge of the application of medical devices for clinical trials, is separately assigned to each site, to maintain the blindness of the blinder. The unblinded investigator does not participate in the research process other than the treatment to minimize the impact on the efficacy and safety evaluation of the investigator, due to an unblinded design.

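### Offering the extension only to the two active groups reveals sham versus active status after V12, so later sham comparisons are not double-blind and some later allocations may become predictable

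*Protocol article*

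**What the plan says.** All references are to the protocol article.

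- **Blinding claim.** Section 2.1 describes "a parallel group, double-blind, multicenter, phase 2 feasibility study".
- **Extension.** Section 2.6.1 says that the opt-tDCS and con-tDCS groups, "but not the sham-tDCS group, will receive the opportunity to provide additional written consent for an extension study". For those who consent, "the extension study will be conducted for two additional weeks".
- **Unblinded role.** Section 2.7 provides one unblinded device investigator per site: "The unblinded investigator does not participate in the research process other than the treatment". It does not mention the extension offer.
- **Timing.** The primary outcome is the FMA-UE change at 2 weeks (Section 2.8). Table 1 has outcomes at V12, the second consent in the V13–V17 column, and the next outcomes at V23. Section 2.11 bases the secondary analyses on change at 4 weeks. Adverse events are recorded through V23.
- **Allocation.** Section 2.5 specifies 1:1:1 block randomization, with two FMA-UE levels and two onset levels. No block size is given. It adds: "A sealed envelope was given to the coordinator of the physical therapy area to identify the group for each participant".
- **Accrual.** Section 2.11 plans 42 patients over 30 months.

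**The concern.** Being offered the extension is a marker of allocation: offered means active, not offered means sham. Patients who know the design can read their own status from it, and so can any member of staff who sees the offer or the absence of one. This follows from a rule the plan states, so fuller procedures elsewhere could limit who sees the marker but could not remove it.

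Two things are at stake. First, sham comparisons on data collected after V12 rest partly on performance measures such as the WMFT, BBT and ADL, and on reported adverse events, all of which expectation can influence. The plan nevertheless carries its double-blind label over the whole trial. Second, in a blocked list each revealed patient narrows what remains in that block. A recruiter who can work out that the next patient will, or will not, receive sham could enrol selectively. That is the only route by which the offer itself could reach the primary endpoint.

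**Working it through.** The plan gives no figure on this point to reproduce, so the check has two parts.

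**1. Which data are exposed**

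| Data | Relative to the offer | Sham vs active | Opt vs con |
|---|---|---|---|
| Patient's own FMA-UE at V12 | before | not revealed | not revealed |
| 4-week secondary outcomes, V23, later adverse events | after | revealed | not revealed by the offer |

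**2. How far earlier offers predict later allocations**

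Inputs from the plan: 1:1:1 blocks, 2 × 2 = 4 strata, 42 patients, 30 months, two sites. Assumptions: block size 3, 6 or 9; status revealed 14 days after randomization (the two-week course); a recruiter who knows the stratum, the block size and the position in the block.

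*Ceiling: every earlier patient in the block already revealed.* The recruiter guesses active unless sham is more likely, and a tie counts as half.

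Blocks of 3 (one sham):

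| Sham position | Allocations certain in advance | Expected correct guesses of 3 |
|---|---|---|
| 1st | 2 (2nd and 3rd) | 2 |
| 2nd | 1 (3rd) | 2.5 |
| 3rd | 1 (3rd) | 2.5 |

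Certain: 4/9 = 44.4%. Correct guesses: 7/9 = 77.8%.

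Blocks of 6 (two shams; 15 arrangements × 6 positions = 90). Let j be the position of the second sham.
- Every position after j is certainly active. Summing (j − 1)(6 − j) over j = 2 to 5 gives 4 + 6 + 6 + 4 = 20.
- When j = 6 (5 arrangements) the last position is certainly sham, which adds 5.
- When the shams are 5th and 6th, the 5th is certain too, which adds 1.
- Total: 26/90 = 28.9%. Correct guesses by the same enumeration: 74.4%.

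Blocks of 9: 21.4% certain, 72.8% correct guesses. With no information, always guessing active is right 2/3 = 66.7% of the time.

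*Is the earlier patient usually revealed in time?* The mean gap within a stratum is 30 × 4/42 = 2.86 months, about 87 days. With exponential gaps, P(gap > 14 days) = exp(−14/87) = 0.85. If lists are also split by site (8 cells) the probability is 0.92.

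*Allowing for the delay and for unfinished blocks.* Simulation of 42 patients arriving uniformly over 25 or 30 months (the shorter period as a sensitivity value), in 4 or 8 equally likely cells, 3,000 runs each:

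| Block size | Certain, ceiling | Certain, simulated |
|---|---|---|
| 3 | 44.4% | 35–36% |
| 6 | 28.9% | 17–21% |
| 9 | 21.4% | 5–14% |

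*If lists are shared across two equal sites and staff see only their own site's offers* (blocks of 3, all own-site patients revealed):
- 1st position: 0.
- 2nd position: the 1st was sham and seen, 1/3 × 1/2 = 1/6.
- 3rd position: the sham came earlier and was seen, 2/3 × 1/2 = 1/3, or both earlier patients were active and both seen, 1/3 × 1/4 = 1/12; together 5/12.
- Average: (0 + 1/6 + 5/12)/3 = 19%.

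**The case against.** Several stronger readings are tempting, and the documents do not support them.

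- *That everything after V12 is open.* The offer goes to both active groups alike, so it does not reveal opt versus con, the comparison on which the Introduction's hypothesis rests. It is also unclear whether sham patients attend V23. Section 2.6.1 keeps them out of the extension, Table 1 marks the extension visits in a row naming all three arms (possibly an effect of how the table was extracted), and Section 2.11 speaks of two groups without naming them. If sham patients do not attend, there is no sham comparison at V23 to bias.
- *That the primary endpoint is unblinded.* Table 1 puts V12 before the second consent. Only selective enrolment of later patients could carry an effect to it.
- *That later allocations are predictable as a matter of course.* The list was made by statisticians not otherwise involved, Section 2.5 describes the sequence as concealed, and nothing says that recruiters know the block size. Not printing it in an article is no defect. The 44% and 29% are ceilings, and the gain in correct guesses is at most 11 percentage points (77.8% against 66.7%).
- *That the envelope is a second leak.* The physical-therapy-area coordinator may be the unblinded device investigator, and a web system can coexist with sealed envelopes. The text does not settle this, so it calls for reconciliation and is not a demonstrated breach.

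These limits narrow the point. What remains is that a stated rule discloses sham versus active status and Section 2.7 has no provision for it. Read literally, Section 2.7 confines the unblinded investigator to treatment, which could leave the second consent to someone meant to stay blind.

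**Conclusion.** The point holds within these limits. Followed as written, the plan discloses sham versus active status once the extension is or is not offered, so the double-blind description does not fit any sham comparison on data after V12. That conclusion needs no assumption about block size. It does require that sham patients contribute data after V12, which the documents leave unclear.

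The predictability of later allocations is a conditional, secondary risk. Under the stated assumptions about block size, delay and what recruiters know, it concerns roughly a third of allocations with blocks of 3 and about a fifth with blocks of 6. It is smaller with larger blocks or with sight of one site only, and it concerns sham versus active alone. The matter is worth correcting but does not invalidate the primary analysis.

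**What to change.** 1. State that V12 is completed and its data locked before anyone learns whether the extension is open to that patient.
2. Keep extension status from enrolling and assessing staff. Amend Section 2.7 so that the already unblinded device investigator may handle the offer. Patients will still know and may tell an assessor, which is why step 4 is also needed.
3. For patients still to be randomized, use randomly varying block sizes that are unknown to the sites.
4. Describe only data up to V12 as double-blind. Report later sham-versus-active comparisons as not blinded, without applying that label to opt versus con.
5. Reconcile Section 2.6.1 with Table 1 on whether sham patients have extension visits, and say whether they attend V23. Reconcile Section 2.5 with Section 2.7 on whether the coordinator who receives the group envelope is the unblinded device investigator.

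Who should receive the extension is a clinical matter and is not addressed here. The cost is minor procedural wording, a re-issued list for remaining patients, and a narrower blinding claim for data after V12. Sample size and endpoints do not change.
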